## Methods

### Study design

LIGHT is a multi-center RCT assessing the (cost-)effectiveness of a 1-year personalized lifestyle intervention as compared to usual healthcare and general health advice with 300 participants. Participating research centers include Maastricht University and Amsterdam University Medical Center. Outcome measurements are conducted at baseline and at the end of the 1-year intervention. LIGHT has been approved by the medical ethical committee of MUMC+ (NL86513.068.24) and is registered at Dutch trial register OMON (NL-OMON57198) and ClinicalTrials.gov (NCT06832761, registration date February 18th 2025). This study will be conducted in accordance with the ethical conduct and juridical laws of the Declaration of Helsinki (2013), Good Clinical Practice (GCP) as defined by the International Conference on Harmonization (ICH) Guidelines, and the Medical Research Involving Human Subjects Act (WMO). Results will be reported in line with the Consolidated Standards Of Reporting Trials (CONSORT) guidelines [21].

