### Baseline and outcome measurement

All study participants undergo a baseline measurement and one follow-up outcome measurement at 12 months at the research site. Measurements include an assessment of demographics, medical history and medication, cognitive testing, clinical measures, blood sampling and questionnaires. In total, research visits take up to 1.5 h. Table 1 gives an overview of all primary and secondary outcomes.

**Table 1 Tab1:** LIGHT data collection

Measures	Type of outcome

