### Sample size

For power calculation, we used mean scores of the primary outcome, the LIBRA2 score, in people with SCD and MCI as reported in a previous study [31]. A 1-point difference in LIBRA2 scores between the intervention and control group at the end of the study would translate into a Cohen’s d = 0.35. To detect such a small to moderate effect size with 80% power in two-sided testing at an alpha-level of 0.05 and a 1:1 treatment allocation ratio, 133 patients per group are needed. Further assuming a 10% dropout rate during the trial means that we need 148 participants per group, resulting in a total sample size of 296, which was rounded up to 300.

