#### Effectiveness analysis

We will use linear mixed model analyses to test the effect of the intervention on the primary and secondary outcome variables (except secondary measures collected for process evaluation and cost-effectiveness) as these models generally handle missing outcome data well and thereby align with the intention-to-treat principle, even if only baseline values are available [63]. Models will use a random intercept (individuals) and, if likelihood ratio testing suggests better fit, random slopes (time). Treatment group (intervention or control) and time (baseline and 1-year follow-up) will be included as fixed effects, and study site and diagnostic group (SCD or MCI) as fixed covariates. Additional covariates will be added if randomization was not successful in balancing other characteristics (e.g. age, gender and education) between treatment groups. An interaction term between treatment group and time will be included as fixed effect. The intention-to-treat principle is used by including all randomized participants in the analyses, including dropouts and non-adherent participants. Missing primary and secondary outcome data are considered as missing-at-random (i.e., missingness is probabilistic and conditional on the covariates included in the analyses) and handled efficiently through maximum likelihood estimation of expected scores in the linear mixed model [64]. We will additionally assess differences in effectiveness and adherence between the SCD and MCI groups using stratified analysis. All analyses will be two-sided at an alpha level of 0.05 and conducted in Stata 18 or higher. A per-protocol sensitivity analysis will be performed to assess whether results remain consistent when excluding participants with low adherence to the intervention.

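### The likelihood ratio rule for adding random slopes does not fit a design with two visits per participant; one estimable covariance structure should be fixed in advance

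*Protocol article*

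**What the plan says.** The number of measurements is fixed in two places. The Study design section says: "Outcome measurements are conducted at baseline and at the end of the 1-year intervention". The section on baseline and outcome measurement says: "All study participants undergo a baseline measurement and one follow-up outcome measurement at 12 months at the research site".

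The Effectiveness analysis section uses the same two occasions in the model: "time (baseline and 1-year follow-up) will be included as fixed effects", with treatment group alongside. The treatment effect is the group-by-time term: "An interaction term between treatment group and time will be included as fixed effect". For the random part it says: "Models will use a random intercept (individuals) and, if likelihood ratio testing suggests better fit, random slopes (time").

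The rule covers more than the primary outcome: "We will use linear mixed model analyses to test the effect of the intervention on the primary and secondary outcome variables", except the process and cost-effectiveness measures. The section does not say whether intercept and slope may be correlated, how time is coded in the random part, or which reference distribution the likelihood ratio test uses.

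**The concern.** A random slope describes how individuals differ in their rate of change. To separate that from residual noise, a model with constant residual variance normally needs at least three occasions. With two, each person has a single change score, and its variance mixes true slope differences with measurement error.

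The article therefore states a selection rule, for the primary outcome among others, that its own design cannot support in the intended sense. At stake are whether the chosen model is estimable, whether the test has its nominal error rate, and whether the covariance model for the primary analysis should depend on such a test at all.

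**Working it through.** The article gives no figure for this rule, so there is none to reproduce. The inputs are:
- From the article: two visits; group-by-time effect; 300 participants with 10% dropout assumed, or 133 evaluable per group (266 in total); 1 LIBRA2 point equal to d = 0.35, which implies an SD of 1/0.35 = 2.86.
- Assumed for the simulations: correlation 0.7 between visits, and ratios of 12-month SD to baseline SD of 0.7, 0.85, 1.00 and 1.15.

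**1. Counting parameters.** Code time as 0 and 1. Let a be the intercept variance, s the slope variance, c their covariance and e the residual variance. Then
- Var(baseline) = a + e
- Cov = a + c
- Var(12 months) = a + s + 2c + e

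| Random part | Parameters | Rank | Status |
|---|---|---|---|
| Intercept only | 2 | 2 | identified; forces equal visit variances |
| Intercept and slope, independent (c = 0) | 3 | 3 | just identified |
| Intercept and slope, correlated | 4 | 3 | not identified |

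**2. Correlated reading.** Two parameter sets (a, s, c, e) give the same matrix:
- (5.7, 1.0, 0, 2.4): variances 5.7 + 2.4 = 8.1 and 5.7 + 1.0 + 2.4 = 9.1; covariance 5.7.
- (6.7, 3.0, −1.0, 1.4): variances 6.7 + 1.4 = 8.1 and 6.7 + 3.0 − 2.0 + 1.4 = 9.1; covariance 6.7 − 1.0 = 5.7.

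No data can tell them apart. In one simulated trial (300 participants, 10% dropout, SD ratio 1.15), four optimisers reached the same log-likelihood (−1335.4737) with slope variances from 1.00 to 1.79 and residual variances from 1.63 to 2.02. A fifth failed to converge. The model adds two parameters to the random intercept but only one degree of freedom is real (4 − 2 = 2 nominal; 3 − 2 = 1 actual). With equal visit variances (20,000 simulations, 266 complete participants), the test on 2 df rejected 1.4% of the time; on 1 df it rejected 5.2%.

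**3. Independent reading.** With c = 0, Var(12 months) − Var(baseline) = s, which cannot be negative. The test is therefore one of variance increase.
- Equal variances: rejects 2.6% on 1 df, or 5.2% with the boundary mixture reference (20,000 simulations).
- SD ratio 1.15: rejects 89% of the time (same simulation size).
- SD ratio 0.85: rejects in 0% of 60 simulated trials (300 participants, about 10% dropout), whereas an unstructured 2x2 covariance rejected equal variances in 98% of them.

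The result also depends on coding. With 12 months as zero, the direction reverses. With time coded −½ and +½, both variances equal a + s/4 + e and the covariance is a − s/4: three parameters for two quantities, so the model is again not identified.

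**4. Effect on the treatment estimate.** In the single trial above, all four converged fits gave a group-by-time estimate of −0.464 (SE 0.274); intercept only gave −0.467 (SE 0.272). Over 1,000 null trials per setting (300 participants, 10% random dropout, independent reading, z tests), the rule compared with an unstructured covariance as follows:

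| SD ratio | Type I error, rule / unstructured | Mean SE, rule / unstructured |
|---|---|---|
| 0.85 | 5.1% / 5.8% | 0.251 / 0.249 |
| 1.00 | 4.4% / 4.3% | 0.266 / 0.266 |
| 1.15 | 6.2% / 6.0% | 0.292 / 0.292 |

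The Monte Carlo error of each type I rate is about √(0.05 × 0.95 / 1000) = 0.7 percentage points. The largest SE difference in any one trial was 2.7%.

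**5. Where a bias can arise.** For dropouts, the model predicts the 12-month score from baseline with slope Cov/Var(baseline). At SD ratio 0.85 the true slope is 0.7 × 0.85 = 0.595. A random intercept alone averages the two variances and uses about 2 × 0.595 / (1 + 0.85²) = 0.691, an error of 0.096. Bias in the contrast is roughly this error times the between-arm difference in how far dropout shifts the completers' baseline mean. With dropout assumed to depend on baseline differently by arm, simulation gave a bias of about 0.07 points at ratio 0.85 and 0.13 at ratio 0.7; an unstructured covariance was essentially unbiased. A bias of 0.07 needs a baseline shift differing between arms by about 0.07/0.096 = 0.73 points, or 0.73/2.86 = 0.26 SD, which is a strong mechanism.

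**The case against.** A fair defence has four parts.

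First, the article does not commit to correlated effects, and with independent effects and 0/1 coding the model is identified. The covariance structure is also a detail that may sit in an analysis plan that is not shown. This stands against any claim that the slope model is unidentifiable on every reading. It does not rescue the rule, because the independent version tests only for a variance increase.

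Second, the test can be computed, and if it does not reject, or the slope model does not converge, an identified random-intercept model remains. A reader might infer that the rule is inoperable; that is too strong. It runs, but it is miscalibrated or one-directional and answers a different question.

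Third, a reader might infer that the standard error and p-value for the primary outcome are compromised. The documents do not support this. The effect is a fixed within-person contrast. With complete data its standard error depends on the variance of the change score, which a random intercept alone estimates as Var(baseline) + Var(12 months) − 2 Cov even when the visit variances differ. Non-unique components leave the fitted covariance matrix, and hence the inference, unchanged. The simulations agree. This part stands under random dropout.

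Fourth, the remedy is partly preference: a random intercept alone also removes the identification problem. That is true, but with unequal visit variances it carries the possible bias in step 5 of the working.

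**Conclusion.** The point holds in a limited form. Two visits cannot support the stated choice between a random intercept and random slopes. With correlated effects the components are not identified and the nominal 2-df test is too conservative (1.4% against 5%). With independent effects the test detects only a larger 12-month variance. Either way the covariance model for the primary and most secondary outcomes is picked from the data by a test that carries no information about individual slopes, and fitting may fail.

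The parameter count is certain from the design. The sizes rest on an assumed visit correlation of 0.7, the SD implied by d = 0.35, and the SD ratios tried. Under random dropout the group-by-time estimate, its standard error and its type I error barely move. Against the 1-point target, a bias of 0.07 to 0.13 is small, and it needs both unequal visit variances and arm-specific, baseline-dependent dropout. The sample size is not affected. Severity is minor to moderate: worth correcting before analysis, but no reason to doubt the primary comparison.

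**What to change.** Delete the random-slope option and the likelihood ratio test from the Effectiveness analysis section (or override them in the analysis plan), and name one estimable structure for the two visits. The preferred choice is a repeated-measures model with an unstructured 2x2 residual covariance within participant, fitted by REML, with the fixed effects as already stated. It has three parameters for three quantities, allows the 12-month variance to be larger or smaller, and does not depend on time coding. Kenward-Roger degrees of freedom are optional with about 300 participants. If the random intercept alone is kept instead, say so without a selection step and accept the equal-variance assumption.

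The cost is one sentence. No new data and no change in sample size are needed, and the article's stated software ("conducted in Stata 18 or higher") can fit the preferred model.

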### Primary outcome

The primary outcome is the 1-year change in participants’ modifiable dementia risk profile as measured by the LIBRA2 score (Fig. 2). LIBRA2 comprises of 15 modifiable dementia risk and protective factors identified through an umbrella review and expert consensus study: coronary heart disease, diabetes, hypercholesterolemia, hypertension, depression, obesity, smoking, high physical activity, chronic kidney disease, high alcohol intake, high cognitive activity, healthy diet, hearing impairment, sleep disturbances, and social participation [4, 22]. Each of these factors has an assigned weight based on the factor’s relative risk for dementia from meta-analyses as shown in Supplementary Table 1 [23]. Based on the presence or absence of risk or protective factors, these weights are summed to yield a total LIBRA2 score. Higher scores indicate an unhealthier lifestyle profile and a higher risk of dementia, with a total score ranging from − 6.1 to 25.7. LIBRA2 was constructed in 2024 and represents an update of the original LIBRA index, in which three risk- and protective factors were added (hearing impairment, sleep, social participation). The LIBRA index has been extensively validated to predict brain damage, cognitive decline, incident cognitive impairment and dementia in various population-based studies [28–30] and clinical studies in people with SCD or MCI [31, 32]. LIBRA2 is recently validated in the English Longitudinal Study of Ageing and the Maastricht Ageing Study, showing increased overall performance compared to LIBRA [23]. Yet, validation in clinical samples remains to be established. It has also been included as outcome measures in other multidomain intervention studies targeting the general population [14, 16, 33, 34] and the ongoing 2-year multidomain FINGER-NL trial [35], and has been recommended as a surrogate outcome measure in prevention studies by the World Health Organization’s brain health group [36] and the World Wide FINGER group [20]. Table 2 describes the measurement of each LIBRA2 factor in this study, including the cut-offs that will be applied to assess the presence of the risk factors.

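### The primary mixed model lets baseline means differ by arm, so its group-by-time test is an unadjusted change-score comparison that forgoes the precision of baseline adjustment

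*Protocol article*

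**What the plan says.** The Primary outcome section defines the endpoint: "The primary outcome is the 1-year change in participants’ modifiable dementia risk profile as measured by the LIBRA2 score". Baseline and outcome measurement allows two time points: "All study participants undergo a baseline measurement and one follow-up outcome measurement at 12 months at the research site".

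Effectiveness analysis then fixes the model. "Treatment group (intervention or control) and time (baseline and 1-year follow-up) will be included as fixed effects", and "An interaction term between treatment group and time will be included as fixed effect". There is a random intercept per person, with a random slope if a likelihood ratio test favours it. Adjustment is for "study site and diagnostic group (SCD or MCI) as fixed covariates". Beyond that, "Additional covariates will be added if randomization was not successful in balancing other characteristics (e.g. age, gender and education) between treatment groups". Neither baseline LIBRA2 as a covariate nor a common baseline mean for the two arms is mentioned.

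The Sample size section is built on another quantity: "A 1-point difference in LIBRA2 scores between the intervention and control group at the end of the study", equated with d = 0.35 and giving 133 evaluable patients per group. Randomization and blinding places allocation after the baseline visit.

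**The concern.** Baseline is one of the two outcome rows, and the group main effect gives each arm its own baseline mean. The interaction is then the follow-up difference minus the observed baseline difference. Subtracting the whole baseline difference is more correction than is warranted unless ρ is 1. Randomisation already makes the expected baseline difference zero, so estimating it costs precision.

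Two things are at stake.

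- **Precision and power.** The planned contrast is at best as precise as a baseline-adjusted one. At low ρ it is less precise than the plain end-of-study comparison that justified the sample size.
- **Sensitivity to chance imbalance.** If one arm happens to start with higher LIBRA2, regression to the mean moves the change-score estimate. The plan's provision for imbalanced covariates does not cure this. A covariate entered as a time-constant main effect in the random-intercept model leaves the complete-data interaction unchanged.

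The same model is planned for the secondary effectiveness outcomes.

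**Working it through.** **1. Reproducing the plan's figure.** Inputs from Sample size: d = 0.35, two-sided alpha 0.05, 80% power, 1:1 allocation. A two-sample t-test on end-of-study means needs 129.1, so 130 per group; an unrounded d of about 0.345 gives 133. Allowing for dropout, 133/0.9 = 147.8, so 148 per group and 296 in total, rounded up to 300. The stated size is therefore reproduced as a comparison of 12-month means with no baseline adjustment. The implied SD is 1/0.35 = 2.86 points.

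**2. What the planned interaction estimates.** I simulated a complete data set with 133 per arm, ρ = 0.6, unit residual SD, a true effect of −0.35, and site and diagnosis in the model:

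| Analysis | Estimate | SE |
|---|---|---|
| Planned model, group × time | −0.46842 | 0.11418 |
| t-test on change scores | −0.46842 | 0.11418 |
| ANCOVA on baseline | −0.3475 | 0.1036 |
| Mixed model, common baseline mean | −0.3480 | 0.1018 |

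The first two rows are the same estimator.

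**3. Variances.** Assume equal SD at both visits and correlation ρ. With n per arm, the variance of the arm contrast is SD² × (2/n) × k, where:

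- end-of-study difference (used for sizing): k = 1
- change score (planned model): k = 2(1 − ρ)
- baseline-adjusted: k = 1 − ρ²

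The ratio of adjusted to planned is (1 − ρ²)/[2(1 − ρ)] = (1 + ρ)/2. This is never above 1. The planned k exceeds 1 when ρ < 0.5.

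**4. Power.** Power = Φ(0.35/√(2k/133) − 1.96). For k = 1: 0.35/0.1226 = 2.854, and Φ(0.894) = 81%. For the planned model at ρ = 0.3, k = 1.4: 2.854/√1.4 = 2.412, and Φ(0.452) = 67%. For the adjusted analysis at ρ = 0.3, k = 0.91: 2.854/√0.91 = 2.992, and Φ(1.032) = 85%. The document gives no ρ, so the range below is an assumption.

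| ρ | Adjusted/planned variance | Power, planned | Power, adjusted | n per arm for 80%, planned / adjusted |
|---|---|---|---|---|
| 0.3 | 0.65 | 67% | 85% | 180 / 117 |
| 0.4 | 0.70 | 74% | 88% | 154 / 108 |
| 0.5 | 0.75 | 81% | 91% | 129 / 97 |
| 0.6 | 0.80 | 89% | 95% | 103 / 83 |
| 0.7 | 0.85 | 96% | 98% | 77 / 66 |
| 0.8 | 0.90 | 99.5% | 99.7% | 52 / 47 |
| 0.9 | 0.95 | about 100% | about 100% | 26 / 25 |

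At ρ = 0.5 the gain is what 300/0.75 = 400 patients would give under the planned model.

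**5. With dropout.** Using 148 per arm, 10% missing follow-up and 40 simulated trials per ρ, the mean SEs were:

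| ρ | Planned | Change score | Common baseline | ANCOVA |
|---|---|---|---|---|
| 0.5 | 0.121 | 0.123 | 0.107 | 0.107 |
| 0.7 | 0.094 | 0.095 | 0.087 | 0.088 |
| 0.9 | 0.055 | 0.055 | 0.054 | 0.054 |

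The planned model stays close to the change score.

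**6. Chance imbalance.** A baseline difference b shifts the change-score estimate by −(1 − ρ)b. One standard error of b is 2.86 × √(2/133) = 0.35 points. At ρ = 0.5 that is a shift of about 0.18 points against a 1-point target.

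**The case against.** The endpoint is defined as change, and the interaction estimates change without bias over repeated randomisation. On that view nothing is stated wrongly, and baseline adjustment is only a preference about efficiency. The power shortfall depends on ρ below 0.5, which the document does not support. Table 2 scores several LIBRA2 factors on a reported diagnosis or on medication use, and these would rarely reverse within a year. The inclusion criteria leave heart disease, diabetes, kidney disease and hearing off the list of factors modifiable in one year. All this suggests a fairly high ρ, at which the gain is small: 10% of variance at 0.8 and 5% at 0.9.

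Three technical points are added. The change-score identity is exact only with complete follow-up. ANCOVA drops participants who have only a baseline value. A common baseline mean presumes that baseline data are complete before allocation, whereas several LIBRA2 questionnaires are filled in at home with no stated deadline.

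Much of this stands as qualification. The planned analysis is valid, and its cost depends on ρ. The carry-over argument is reasonable but is inference; the behavioural items could pull ρ down, and the secondary outcomes have their own correlations. Dropout barely changes the comparison (step 5). The points about ANCOVA and questionnaire timing belong in the wording of the fix. None of them gives a reason to keep the free baseline difference, because adjustment is at least as precise at every ρ and uses data the trial already collects.

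**Conclusion.** The concern holds. The article names its model explicitly, so this is a stated choice and not a detail left to a fuller plan. With two visits and a free group main effect, that model is a change-score analysis, exactly so with complete data and closely so with 10% dropout.

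The consequence is lost precision and exposure to chance baseline imbalance, not bias. The variance forgone is 35% at ρ = 0.3, 25% at 0.5, 15% at 0.7 and 5% at 0.9. Planned power falls below that of the end-of-study comparison used for sizing only if ρ is under 0.5.

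These sizes assume equal SD at both visits, d = 0.35 and 133 evaluable patients per arm; ρ is an assumed range. The change should be made, though the trial would not be invalid without it.

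**What to change.** Keep the two-visit likelihood model and remove the group main effect, so that both arms share one baseline mean. The fixed effects become time, group × time, the stratification factors (site and diagnosis) and their interactions with time. Use an unstructured 2×2 within-person covariance in place of the choice between random intercept and random slope. Name the 12-month arm contrast as the primary estimate, and use the same form for the continuous secondary outcomes.

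State that the baseline LIBRA2 items, including the home questionnaires, are completed before allocation, since the common baseline mean rests on this.

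ANCOVA of 12-month LIBRA2 on arm, baseline LIBRA2, site and diagnosis gives nearly the same precision and can serve as an alternative. It omits participants without follow-up, so the constrained model fits the plan's intention-to-treat aim better.

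The cost is a short change of analysis wording before unblinding. No new data are needed and the sample size can stay: the end-of-study calculation becomes conservative, because 1 − ρ² is never above 1. Participants with only a baseline value remain in the constrained model.

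### Extra covariates enter the primary model only after observed imbalance and, read naturally, leave the group-by-time estimate all but unchanged; a closed list acting on the 12-month contrast should be fixed in advance

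*Protocol article*

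**What the plan says.** All of this is in the protocol article, under Effectiveness analysis unless noted.

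- Fixed effects: "Treatment group (intervention or control) and time (baseline and 1-year follow-up) will be included as fixed effects".
- Treatment effect: "An interaction term between treatment group and time will be included as fixed effect". No other interaction is named.
- Prespecified adjustment: "study site and diagnostic group (SCD or MCI) as fixed covariates".
- Further adjustment: "Additional covariates will be added if randomization was not successful in balancing other characteristics (e.g. age, gender and education) between treatment groups". No criterion for failed balance is given, and the examples do not close the list.
- Random effects: a random intercept per person, with random slopes if a likelihood ratio test favours them.
- Missing outcomes: handled by maximum likelihood, assumed missing at random given the model's covariates. Participants with only a baseline value stay in.

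Under Sample size, the target is "A 1-point difference in LIBRA2 scores between the intervention and control group at the end of the study", which "would translate into a Cohen’s d = 0.35". Dropout of 10% is expected.

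**The concern.** Two features of the rule work against its purpose.

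First, the trigger. When randomization is carried out properly, any imbalance is chance. What makes a covariate worth adjusting for is how strongly it predicts the outcome, and observed imbalance does not show that. A trigger with no criterion and an open list leaves the primary model undecided until the data are seen.

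Second, the mechanism. The treatment effect is the group-by-time term, which with two visits is a difference in mean change. A baseline characteristic entered as a main effect shifts both visits of a person equally, so it says nothing about change. If the rule fires, the report would call the result adjusted although the treatment estimate is essentially the unadjusted one. The same applies to site and diagnosis as entered.

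At stake are a conditional distortion left in place after an unlucky allocation, some precision forgone, and a misleading label.

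**Working it through.** **Scale of the trial (Sample size section).** With d = 0.35, two-sided alpha 0.05 and 80% power, n per arm = 2(1.960 + 0.842)²/0.35² = 2 × 7.85/0.1225 ≈ 128.2, so 129. The t-test version gives 129.1, so 130. The plan's 133 is within 3% of this. Dropout: 133/0.90 = 147.8, so 148 per arm and 296 in total, as stated. The implied SD is 1/0.35 = 2.86 points. Nothing here needs changing; it gives the scale for what follows.

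**Complete data: algebra.** Let x be a baseline covariate and g the arm.

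- Baseline mean: a + b·g + c·x
- 12-month mean: a + t + (b + d)·g + c·x
- Change D = 12 months minus baseline: t + d·g. The covariate has dropped out.
- Person average M: (a + t/2) + (b + d/2)·g + c·x

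In a random-intercept model D and M are uncorrelated. M has its own free intercept and its own free group coefficient (through a and b), so it carries no information on d. The estimate of d and its standard error therefore come from D alone and do not depend on c·x. For any other 2 × 2 covariance common to all participants, replace M by baseline − k·D, with k chosen so that it is uncorrelated with D; the result is the same. Random slopes therefore do not rescue the rule.

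**Simulation.** N = 300, 60 data sets per scenario, true effect −1. Assumed, not in the documents: within-person correlation about 0.6 given the covariate, imbalance 0.4 SD, covariate slope on level 1 point per SD, and covariate effect on change 0 or 0.8 points per SD. The imbalance is deliberately large. All models contain site and diagnosis as main effects. Entries are mean group-by-time estimates.

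| Scenario | No extra covariate | Added as main effect | Covariate by time |
|---|---|---|---|
| Complete, effect on change 0 | −1.0284 | −1.0284 | −1.0283 |
| Complete, effect on change 0.8 | −0.7166 | −0.7166 | −1.0283 |
| About 10% missing at random draw, 0 | −1.0369 | −1.0381 | −1.0338 |
| About 10% missing at random draw, 0.8 | −0.7210 | −0.7229 | −1.0338 |
| About 11% missing, depending on covariate, 0 | −1.0378 | −1.0347 | −1.0372 |
| About 11% missing, depending on covariate, 0.8 | −0.7308 | −0.7262 | −1.0372 |

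With complete data the largest difference between the first two columns in any data set was 0.000000, and the mean standard error was the same in both (0.2933 with effect 0; 0.3068 with effect 0.8). With missing follow-up the mean shift was at most 0.005 points, and the largest single shift was 0.04 to 0.07 points, against a standard error of about 0.31 to 0.32. A separate run of 50 trials with an unstructured covariance (133 per arm, imbalance 0.3 SD, 0.8 points per SD) gave −0.728 with and without the main effect, and −0.997 with covariate by time.

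**Realistic size.** The SD of a chance standardised imbalance with 133 per arm is √(2/133) = 0.12. With the assumed 0.8 points per SD, the uncorrected shift is 0.12 × 0.8 ≈ 0.1 point. The 0.4 SD used above is 0.4/0.12 ≈ 3.3 of these SDs, so the table shows the mechanism and not a likely size.

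**The trigger.** If three independent characteristics were each tested at 5%, the chance of at least one false alarm would be 1 − 0.95³ = 14.3%. This is illustrative, since the article names no test.

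**The case against.** Several counter-arguments have force.

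- *The two complaints partly offset each other.* If main-effect covariates hardly move the estimate, the analyst cannot steer it by choosing them. This stands: on the natural reading the practical harm of the discretion is small. It becomes real if the covariates are entered in a way that acts on change, which the article does not rule out.
- *Main-effect entry is inferred.* For the extra covariates the article says only that they are added, and an analysis plan may give exact terms, a criterion and a closed list. This stands as a limit on certainty. But the article does state a rule, with a single named interaction, and that rule is what is criticised.
- *Covariates also support the missing-data assumption.* True, so they are not without function.
- *Site and diagnosis are balanced by stratified blocks.* True, so little imbalance remains to be corrected for these two. What is forgone is at most some precision.

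A reader might infer that added covariates can never change the treatment effect. The exact result needs complete data; with the planned dropout, shifts of a few hundredths of a point occur. A reader might also infer that the trial's estimate is biased. Under randomization a chance imbalance does not bias the unadjusted contrast on average, and its variation is reflected in the standard error; the distortion is conditional on an unlucky draw. Finally, a large correction, such as half a point, is not supported: it needs both an unusual imbalance and a strong covariate effect on change, and the documents give no such effect.

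**Conclusion.** The point holds in limited form. The rule ties the primary model to observed imbalance and, as naturally read, does not deliver the correction it is meant to provide. The cancellation with complete data is exact and needs no assumed values beyond main-effect entry and a model that keeps the group main effect, as this one does. The size of what is left uncorrected does depend on assumptions: about 0.1 point for a typical imbalance at 0.8 points per SD, none if the covariate does not affect change, and more for rarer imbalances or stronger effects. The validity of the randomized comparison is not in doubt. This is a weakness worth repairing before the analysis, not a threat to the trial.

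**What to change.** 1. Delete the rule that makes adjustment depend on observed balance.
2. Fix a short closed list now: site and diagnosis as stratification factors plus, for example, age, sex and education, used whatever the balance turns out to be. The choice should rest on expected prognostic value. The documents do not show that these three predict change in LIBRA2, so the sponsor should confirm the list.
3. State how the covariates enter, so that they act on the 12-month contrast. One option is a model for the 12-month score with baseline LIBRA2 and the covariates (ANCOVA). Another is covariate-by-time terms in the mixed model. If a constrained-baseline model is chosen, it should carry covariate-by-time terms too: with the covariate as a main effect only, the simulation with complete data and 0.8 points per SD gave −0.78 against a true −1.

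The change is wording only. Stratification already uses centre and diagnosis, and the other characteristics are collected at baseline. It costs a few degrees of freedom, and a covariate that does not affect change can slightly widen the interval (standard error 0.2933 to 0.2992 in the complete-data simulation with the large 0.4 SD imbalance). The sample size is unaffected.
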